# CLINICAL EVALUATION INCLUDING AYURVEDIC ASSESSMENT

Both Allopathic and Ayurvedic physicians, and predesignated study personnel will carry out assessment of all study patients as per the study schedule of events and timelines shown in Fig 1. and in Appendix A.

Several of the patient centric assessments including health and quality of life measures will be completed by the study paramedic without the knowledge of the drug allocation of the patient (assessor blind).

Standard study case record forms will be used on patient enrolment (baseline) to record patient data and will included demographics, personal habits, comprehensive medical history and examinations, measures of health and quality of life (Appendix H). The Ayurveda physician will also record the required clinical parameters of the study patient in the Ayurveda Case Record Form (Appendix I).

The routine hospital case record sheet will be used to record the patient’s progress while in hospital. The study investigator and the Ayurvedic physician will extract the relevant data of the patient from the hospital case sheet on a daily basis and enter it into the ‘study progress sheet’. (Appendix J).

On completion of treatment and at time of discharge, the investigators will complete the study completion case record form which will also include parameters on outcome (recovery or death) (Appendix K). The study patients will be provided with a precise follow-up schedule for the post treatment evaluation and during which the patients will be assessed as per schedule of events (Table 1) at weeks 4, 8 and 12 (study completion). It should be noted that some patients may require a longer period to recover that may extend from 3-4 weeks and in which case the assessment at discharge will also comply with the requirements of week-4 time endpoint (see Table 1).

During the study period, the study patient will complete a self-reported questionnaire on COVID 19 related symptoms daily which will be provided in the form of a mobile application. The self-reported questionnaire is enclosed in Appendix L.

All patients withdrawn for any reason will complete a medical examination and complete other documents as required on study completion (see above). If possible, laboratory evaluation as described above for study completion will also be done.

Laboratory and imaging investigations will be carried out as per Table 1 and are further described below.

It should be noted that study investigators will work closely with the hospital physicians in a co-operative and positive manner so as to offer the best possible management to the patient and avoid any unnecessary discomfort of any kind to the patient arising from study participation. It is prudent to state that while the success of clinical drug trials usually depends upon strict compliance with the requirements stated in the study protocol with particular reference to Schedule of Events, see Table 1), the interest of the patient and his/her wellbeing is of topmost priority and the investigators may use their judgment and discretion to modify the study requirements to serve that purpose. However, the latter will be a protocol deviation and clearly recorded by the senior study investigator with an explanatory note on its compulsion in the study completion case record form.

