**Note:**

- Each study site shall have at least two Principal Investigators, one each from Ayurevda and modern medicine.
- Additional study sites and PIs may be added based on clearances from respective IECs

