**f. Study design:**

This is a prospective, randomized, open label, blinded end point (PROBE), parallel efficacy, multicentric, two arm study to compare the efficacy of a combination of Standard of Care (SOC) plus a selected individual Ayurveda herbal drug (Samshamani Vati Plus or AYUSH 64 or Yashtimadhu) to SOC (active control). The Ayurveda drug is being considered as an adjunctive or an add-on therapy and each of the three drugs will be evaluated in separate two arm trial with a common study design. The drug trials are ‘exploratory’ in design. The Study Flow diagram summarizes the study design and schedule of events (Fig 1) (Appendix A).

**g. Sample size:** The total sample size is 140 patients per drug trial- 70 patients in each arm.

**h. Study Population:** All adult patients with laboratory-confirmed SARS-CoV2 infection with mild to moderate category will be selected from the outpatient or inpatient facility in COVID-19 medical centers/hospitals. Voluntary patients will be explained about the study and if willing will sign the informed consent and be screened for eligibility.

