Both Ayurvedic and Allopathic Physicians will jointly examine and monitor study participants in addition to the hospital treating physician

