# CONSENT, SELECTION, SCREENING, and ENROLLMENT

Study patients will be served on first come first serve basis as per the protocol.

Consenting and eligible patients will be enrolled as soon as possible in a COCID-19 management facility and the study intervention begun. It is important that symptomatic patients suspected for COVID-19 on clinical grounds are quickly evaluated for eligibility. It is important to enroll the patient as close to the onset of symptoms as possible. As described above, this study is dealing with patients of COVID who are ‘non-emergent’ which means mild and moderate disease (pneumonia) which does not require emergency or critical care (see section on inclusion and exclusion criteria).

An ‘Patient Information Sheet’ (Appendix F) in the language understood by the patient will be provided to each patient for study and discussion prior to enrollment. The information fact sheet will describe the overall design of the study and the rationale, benefit and side effect profile of the study drug interventions, and other aspects of the study.

Patients will be selected from the outpatient or inpatient facility in COVID-19 medical centres/ hospitals. The study will be explained to the volunteer patients and those willing to sign the informed consent (Appendix G) will be screened for eligibility as per the inclusion and exclusion criteria in the protocol.

Though it will be preferable to enrol patients with diagnosis confirmed by a positive RT-PCR assay using a nasal or throat swab in a standardized procedure, a patient with a clinical diagnosis of COVID- 19 as described below will be eligible.

Eligible patients will be enrolled using a simple randomization table (provided to the investigator) in a block of 20 patients each to either of the two study arms - SOC plus Ayurveda drug or SOC. As the target sample size is 70 patients in each arm, the first block of randomized allocation will be of 10. The study randomization will be carried out by the investigator.

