**Criteria of ‘Clinical Recovery’**:

1. Normal body temperature (≤36.6°C axilla or ≤37.2 °C oral)
2. Absence of cough or mild cough (infrequent, short episodic, non-wheezy, relieved by minimal or no medication, not interfering with routine speech and not related to lying in bed, mild sore throat or nasal congestion)
3. Absence of breathlessness on routine daily self-care chore or respiratory rate less than 30 breaths per minute without supplemental oxygen
4. Absence of any other symptom/sign attributed to COVID-19 illness
5. Normalization of SpO2 by standard peripheral oximetry device (above 95 percent)
6. Recovery should be sustained for at least 48 hours under physician observation
7. Assessed by physician blinded to treatment allocation
8. All of the above criteria ought to be fulfilled

Note: Clinical recovery would be deemed from the first day of satisfying the above criteria

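### Blinded assessment of clinical recovery is required but not put into operation, and the described workflow contradicts it

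*Combined protocol and SAP*

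**What the plan says.** The synopsis (f. Study design) states: "This is a prospective, randomized, open label, blinded end point (PROBE), parallel efficacy". Among the criteria of clinical recovery, in the synopsis and in Section 11.1, is "Assessed by physician blinded to treatment allocation", and all the criteria must be met. Both primary outcomes, time to clinical recovery and the proportion recovered, use this definition.

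The procedures are described elsewhere:

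- **Randomisation** (Consent, Selection, Screening, and Enrollment): "Eligible patients will be enrolled using a simple randomization table (provided to the investigator) in a block of 20 patients each", and "The study randomization will be carried out by the investigator".
- **Examination** (note to Fig 1): "Both Ayurvedic and Allopathic Physicians will jointly examine and monitor study participants in addition to the hospital treating physician". The clinical evaluation section adds: "Both Allopathic and Ayurvedic physicians, and predesignated study personnel will carry out assessment of all study patients".
- **Dosing** (synopsis, k. Medication; Section 3.1): the Ayurvedic physician may change the dose of the study drug.
- **Daily record** (clinical evaluation section): "The study investigator and the Ayurvedic physician will extract the relevant data of the patient from the hospital case sheet on a daily basis", for entry in the progress sheet (Appendix J). That sheet carries fever, cough, dyspnoea, respiratory rate and oxygen saturation.
- **Outcome** (same section; Appendix K): the investigators complete the completion form, including recovery or death, and an investigator signs it.
- **Staffing** (note on study sites): "Each study site shall have at least two Principal Investigators, one each from Ayurevda and modern medicine".

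The only role described as working without knowledge of the arm is the study paramedic, for patient-centred and quality-of-life measures.

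**The concern.** In an open-label trial without placebo, a blinded assessor is what separates PROBE from an ordinary open design. Several recovery criteria are judgements: whether a remaining cough counts as mild, whether breathlessness is absent, and whether any other symptom or sign is attributable to COVID-19. Recovery is then dated to the day, so a small tendency to call it earlier in one arm feeds directly into the primary comparison.

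If the workflow is followed as written, people who know the arm, or are well placed to know it, examine the patient, compile the recovery components and sign the outcome. A reader of the results would be told that the end point was blinded and could not verify it from the forms.

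**Working it through.** **1. Tracing the roles.** The plan gives no figure to reproduce on this point, so the first check is who does what.

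| Step | Who does it | Knows the arm? |
|---|---|---|
| Holds randomisation table, randomises | Investigator | Yes |
| May change study-drug dose | Ayurvedic physician | Yes, by necessity |
| Joint examination | Ayurvedic and allopathic physicians | Ayurvedic: yes. Allopathic: inferred, not stated |
| Daily symptoms and vital signs (Appendix A footnote) | A physician | Not stated |
| Daily extraction to Appendix J | Study investigator and Ayurvedic physician | Ayurvedic: yes. Investigator: yes, if the one who randomises |
| Outcome form, Appendix K | Investigators complete, an investigator signs | Yes, for the one who randomises |
| Blinded judgement of recovery | A physician, otherwise unidentified | Must not, but no procedure secures it |

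Appendix K has no field for a blinded assessor and none for the date of recovery. It does ask about interruptions of the investigational drug. The arm and drug names are on the cover of the enrolment case record form (Appendix H). The patient carries a card indicating study medication (Section 19.2), and the app sends suspected side effects to the local investigator every day (Section 19.3).

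**2. Illustration of what a small shift would do.** The protocol states no SD. Inputs:

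- Recovery IQR 7 to 14 days (Table 2, Time to outcome), from one retrospective hospital cohort. Assuming rough normality, SD = (14 − 7)/1.349 = 5.19 days. Because that cohort was not restricted to mild-to-moderate disease, a range of 4 to 7 days is used.
- 70 per arm (Section 17.1). With the upper assumed withdrawal of 20%, 70 × 0.8 = 56 per arm.
- Two-sided α = 0.05 (Section 17.2), no true effect, two-sample normal test.
- Spurious shift b of 0.5 or 1 day. This is an assumption with no source in the documents.

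SE = SD × √(2/n). Rejection probability = 1 − Φ(1.96 − b/SE) + Φ(−1.96 − b/SE).

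Example: SD 5.19, n = 70 gives SE = 5.19 × √(2/70) = 0.877. For b = 1, b/SE = 1.14, and the rejection probability is 20.7%.

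| SD (days) | n per arm | SE | b = 0.5 day | b = 1 day |
|---|---|---|---|---|
| 4 | 70 | 0.676 | 11.5% | 31.6% |
| 4 | 56 | 0.756 | 10.1% | 26.3% |
| 5.19 | 70 | 0.877 | 8.8% | 20.7% |
| 5.19 | 56 | 0.981 | 8.0% | 17.5% |
| 7 | 70 | 1.183 | 7.1% | 13.5% |
| 7 | 56 | 1.323 | 6.7% | 11.8% |

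This concerns the time outcome only. No corresponding figure was computed for the proportion recovered.

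**The case against.** The blinding criterion is part of the end-point definition, so a recovery judged unblinded does not formally qualify. A separate blinded physician is not excluded: sites have at least two principal investigators and other predesignated personnel. Section 19.12 refers to standard operating procedures that are not among the documents and might name an assessor. All of this stands. A reader might infer that blinding is defeated outright, or that nobody at a site is blind; the documents do not support either, and the paramedic is expressly blind.

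The daily extraction is transcription from the hospital case sheet, not a judgement of recovery, and monitors check it against source data. That also stands; the outcome form is the stronger evidence. Nor is the investigator who randomises shown to be the same person who extracts the data or signs.

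It is tempting to call blinded assessment the only protection of the primary outcomes. It is not: temperature and oxygen-saturation limits, a respiratory-rate limit (as an alternative to absence of breathlessness) and the 48-hour rule also help.

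It is equally tempting to say that the staff listed make the remedy free. The documents do not show that. The paramedic is not a physician, and investigators also judge drug causality, receive serious adverse event reports and app alerts, and countersign case record forms.

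Finally, the trial is declared exploratory and unpowered. That limits what will be claimed from it but does not excuse labelling an end point blinded when no procedure makes it so.

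**Conclusion.** The concern holds as a failure to put blinding into operation, combined with a workflow that contradicts it. This goes beyond missing detail, because the described steps place the recording of the primary outcome with investigators, and an investigator carries out the allocation. Two links are inferred: that the allopathic physician knows the arm, and that the investigator's roles fall to the same person.

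The procedural finding does not depend on the arithmetic. The illustrated inflation, from 5% to about 7–11.5% for a half-day shift and about 12–32% for a one-day shift, rests on an assumed SD and assumed shifts; it shows sensitivity and does not predict the bias in this trial. Part of any such shift could also come from unblinded patients' own symptom reports. The sponsor should correct this, and the change is modest.

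**What to change.** - **Separate the roles.** Assign randomisation, dispensing, dosing decisions, the medication log, drug-causality judgements, serious adverse event handling and review of app side-effect reports to the Ayurveda principal investigator or another unblinded investigator at the site. Arrange countersignature of case record forms so that it does not unblind the assessor.
- **Name the assessor.** Designate one existing physician per site with none of those duties. That physician examines for recovery separately from the joint examination, and completes and dates a recovery form that does not show the arm. Ask patients not to disclose treatment or show the study card at that assessment.
- **Change the forms.** Move study group and drug names from the case record form cover to the dispensing log.
- **Specify the analysis.** Derive the recovery date by one algorithm from the recorded components. Add a sensitivity analysis on the objective components: temperature, respiratory rate and oxygen saturation.
- **Report honestly.** Where a site cannot separate the roles, report its recovery assessments as unblinded and do not describe them as PROBE.

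The cost is protocol wording, form changes and some scheduling. Each site must confirm that it has a physician free of the unblinding duties. Bias from patients' own symptom reports will remain, which is why the sensitivity analysis is needed.

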# 8. STUDY DURATION, FOLLOW- UP SCHEDULE AND PROCEDURES

This is summarized in Figure 1 and Table 1. There are several foot notes provided in Table 1 to further clarify a particular event/test procedure and often with particular reference to the role of the study investigator. Several of the clinical events with reference to clinical examination, study record forms and questionnaires, study procedures, laboratory diagnostics and assessments are elaborated in Appendices enclosed with the protocol (Appendix A to S).

It should be noted that this is a study treatment protocol and that the time to outcome in terms of recovery following onset of illness and/or admission to hospital is a varying parameter. The large majority of study patients are expected to recover completely but based on prior knowledge the mortality of COVID-19 in severe case in well documented (see literature review, section above). It is expected that the majority of patients will recover and be discharged to home within 5 days to 15 days of hospitalization.

However, all study patients who recover are required to follow with the study investigators on pre-determined time points as shown in Table 1.

The total duration of the study is 12 weeks and includes the duration of treatment and post clinical recovery or post-hospital discharge period to ensure optimum recovery and regain of health status.

# 9.WITHDRAWAL AND PREMATURE TERMINATION

The patient can withdraw from the study at any point of time without assigning any reason.

The study investigator can also withdraw the patient for reasons arising out of the study drug intervention such as- intervention treatment failure, progression to severe disease, requirement of critical support care (ICU), requirement of persistent oxygen support, need for ventilation, drug related toxicity, protocol violations etc. All patients withdrawing from the study will be requested to complete the formalities (including laboratory evaluation) of study completion case record form and outcome/ hospital discharge. However, they will be encouraged to continue the clinical and other assessments enumerated for post treatment study schedule in Table 1.

There are several other reasons for patient to withdraw from the study such as:

1. Patients who worsen or need ICU admission or ventilator support due to any reason
2. Non-compliance of the treatment regimen
3. Participants not willing to continue the study
4. Drug related toxicity
5. Any serious adverse event that makes the participant unable to do the activities of daily living / any SAE
6. Any other serious medical condition which the participant may acquire during the course of the trial which makes it difficult for the participant to continue in the trial
7. Any other condition which the investigator feels might cause harm to the participant

All adverse events (AE), and in particular serious adverse event (SAE) will be dealt with as described in the section on AE (see below).

The study investigator s will be required to keep an informal contact with such a study patient uptp the study completion at 12 weeks and record post study withdrawal clinical developments. The probable outcomes of such a study patient will be stated in the case record form and include asymptomatic status, days of hospitalization, symptomatic disease and its severity, time to discharge, time to recovery, death, post recovery status as stated in the patient completion case record form and outcome report

# 10. PATIENT POPULATION

The patients will be largely drawn from COVID-19 clinics and outpatients in various medical colleges and hospitals. All patients will be admitted in the hospital for standard care and those willing to participate in the study will be screened and enrolled as described above. Only patients with mild to moderately severe symptoms will be selected as described above. If the patients progress to a severe stage of illness as described below, they will be withdrawn from the study but the investigator will be encouraged to follow the patient ill study completion at week 12 and during this period record the hospital management, course of illness , final outcome and post recovery health status as described in this protocol.

- 1. Inclusion Criteria:

1. Typical Clinical presentation of acute onset febrile illness with cough and a RT_PCR based laboratory confirmation test for COVID-19
2. Patients with either sex, 21to 69years age
3. Patients with Mild to Moderate COVID-19 as described below
4. All patients must agree not to share medication
5. Patients willing to participate and sign an informed consent
   Note: The criteria for mild to moderate COVID-19 are based on the WHO recommendations (See Section 2.5 above with WHO Table on clinical syndromes of COVID-19 and include Mild disease and Uncomplicated Pneumonia but not severe disease which requires any form of intensive care such as invasive techniques for supplemental oxygen or ventilation and life support systems, and absence of any life threatening complications (such as severe respiratory failure, adult respiratory distress syndrome, septicaemia shock and other complications shown in Table 3 above)
   1. Exclusion Criteria
6. Patients suffering from severe COVID-19 Disease as described above in Section 10.1 and judged by a physician; further guidance can be taken to exclude patient in a clinical context of progressive respiratory dysfunction and failure from the following criteria (i) Respiratory distress at room ambience (≥30 breaths per min) (ii) Oxygen saturation at rest ≤93% (peripheral digital arterial oxymetry) and requiring oxygen support for over one hour to normalize (iii) Any of the known COVID-19 complications and emergency procedures which may require shift/admission in intensive care unit such as respiratory failure, adult respiratory distress syndrome, requirement of oxygen support for over 1 hour, requirement of mechanical ventilation, septic shock, or severe non-respiratory organ dysfunction or failure.(62)
   (Adapted and modified from the reference: Yang Liu et al.Lancet Infect Dis 2020 , March 19, 2020 https://doi.org/10.1016/ S1473-3099(20)30232-2)
7. Chronic, Severe, Unstable, Uncontrolled co-existent medical illness such as Diabetes, Hypertension, Cardiac disorders, liver, kidney disorders and lung disorders or other disease of concern which may put the patient at increased risk during the study
8. History of immunosuppression: solid organ or bone marrow transplant, use of immunosuppressive antimetabolic and biologic agents, intrinsic immunodeficiencies, HIV infection.
9. Active cancer diagnosis, on palliative treatment or requiring current therapy with antimetabolic agents, immunotherapy or radiotherapy.
10. Patients on parenteral nutrition
11. Patients with known sensitivity or contraindication to any of the ingredients of study medication
12. History of bleeding haemorrhoids, haemoptysis, acid peptic diseases, ulcers and pulmonary diseases (tuberculosis, asthma, etc)
13. Patients who are likely to worsen or planed ICU admission or ventilator support due to any reason
14. Pregnancy and lactation
15. Participation in a drug interventional clinical drug trial of any nature in the three-month period preceding onset of COVID-19
16. Participation in any other clinical trial of an experimental agent treatment for COVID-19
17. Patients on any kind of Ayurveda treatment or any other alternative and complementary medicinal systems such as Homeopathy, Unani, Siddha and in particular requiring oral therapy of any kind
18. Patients receiving any other test drug, apart from SOC.
19. Physician decision that involvement in the study is not in the patient´s best interest

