The total study period is 12 weeks; Primary Efficacy is ‘Clinical Recovery’ as described in the protocol; Study participant developing severe COVID 19 or severe complication and requiring special critical support/ ICU/ ventilator support will be withdrawn from the study but followed up to record outcome; Both Ayurvedic and Allopathic Physicians will jointly examine and monitor study participants in addition to the hospital treating physician.

Patients will be selected from the outpatient or inpatient facility in COVID-19 medical centres/hospitals. The study will be explained to the volunteer patients and those willing to sign the informed consent will be screened for eligibility as per the inclusion and exclusion criteria in the protocol. Patient suffering from severe COVID-19 will be excluded (see exclusion criteria below).

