**11.2 Secondary Efficacy:**

1) Rate of patients with negative SARS-CoV-2 on nasal or throat swab in a 2-day continuous real time RT-PCR test beginning from ‘first day of clinical recovery’ (see above) or ‘Day 10 after onset of symptoms depending on whichever of the two time points is first achieved

2) Timelines (days counted from onset of illness) - normal body temperature <37◦C, absence or minimal cough (see ‘clinical recovery’ for the definition), absence of dyspnoea (respiration rate 24/minute or less on room air), onset of clinical pneumonia, pneumonia diagnosed on chest X-Ray or CT scan, time to supplemental oxygen, admit in intensive care unit, mechanical ventilation (non-invasive), mechanical ventilation (invasive), steroid use, respiratory failure, adult respiratory distress syndrome, cytokine storm syndrome, secondary infection, shock, septicaemia shock, hospital discharge, death, negative nose or throat swab confirmatory test, all-cause mortality (Time Frame: up to 28 days).

Note: In case of symptoms, the absence on improvement should be sustained for at least 72 hours or live hospital discharge, whichever comes first.

3) Proportion OF patients developing an event that reflects clinical or otherwise improvement of worsening (the events are similar to those listed under Timelines, see above)

4) Improvement on pulmonary function tests using simple ‘home expiratory spirometer’ device and peripheral pulse oximetry

5) Improvement in selected laboratory parameters: blood haemoglobin, differential and total leukocyte counts, liver enzymes, renal functions, acute phase reactants, serum IL-6 and other selected cytokines, serum muscle enzymes (CK, CPK), serum ferritin, serum d-Dimer, anti-oxidant markers, serum BNP (cardiac function)

6) Serological Protective Antibody Assay (IgM and IgG)

7) Radiological Improvement on digital chest Xray and HRCT chest

8) Drug related: side effects and toxicity, and tolerability

9) Health status: WHO QOL (Appendix M) brief, health related behaviour habit and fitness questionnaire based on visual analogue scale (See Appendix N)

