# 14. SAFETY ISSUES AND ENDPOINTS, ADVERSE EVENTS

All adverse events will be recorded and meticulously followed till resolution. Serious adverse events will require immediate action and further communication by the study investigator. AE will be classified by the study physician as described in Appendix P and classified as shown in Appendix Q and recorded in the AE form by the investigator along with its grading (Appendix R).

A-priori check list of common drug related side as a ready reckoner will be provided to all investigators so that timely action may be taken if a patient reports any kind of adverse event that may be related to the study intervention. The patients will be encouraged to record any kind of symptom that they may think is due to a drug in their personal diary which will be scrutinized by the study physician at monthly visits and on completion.

The following ‘**Stop rules’** will be applied to withdraw the patient prematurely because of safety concerns:

1. Patients developing severe COVID-19 as described above under the ‘exclusion criteria’
2. Requiring hospitalization for disorders other than COVID-19 will be critically evaluated by the study physician to decide continuity in the study
3. Any adverse clinical or lab profile that in the opinion of the investigator is likely to be due to therapeutic intervention and threatens to deteriorate the wellbeing of the patients

Data Safety Monitoring Board (DSMB) will be established to monitor safety of the participants and assess safety data. The CONSORT extension for HARMS will be used to document and report safety data.

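### Patients are withdrawn from the study when COVID-19 becomes severe, and the rules for capturing their later severe events and deaths, which are secondary outcomes, are inconsistent and incomplete

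*Combined protocol and SAP*

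**What the plan says.** **Withdrawal at progression.** The Fig 1 note (Synopsis and Section 5) says that participants who become severe or need critical, ICU or ventilator support "will be withdrawn from the study but followed up to record outcome". Section 10 says "they will be withdrawn from the study but the investigator will be encouraged to follow the patient ill study completion at week 12". Stop rule 1 in Section 14 withdraws patients who meet the severe-disease description in the exclusion criteria. Those criteria include "requirement of oxygen support for over 1 hour, requirement of mechanical ventilation, septic shock, or severe non-respiratory organ dysfunction or failure". Section 9 is softer: the investigator can withdraw such patients.

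**Outcomes.** Section 11.2 item 2 lists, among others, "time to supplemental oxygen, admit in intensive care unit, mechanical ventilation (non-invasive), mechanical ventilation (invasive), steroid use, respiratory failure, adult respiratory distress syndrome". It goes on to shock and all-cause mortality, with a time frame of up to 28 days. Item 3 takes the proportions of patients with the same events.

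**After withdrawal.** Under Section 9, investigators "will be required to keep an informal contact with such a study patient" until 12 weeks and must record clinical developments. For the scheduled assessments, however, "they will be encouraged to continue the clinical and other assessments enumerated for post treatment study schedule in Table 1". Section 8, by contrast, makes follow-up at the set time points a requirement for patients who recover.

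**The concern.** The events that Section 11.2 wants to time and count are largely the events that take a patient out of the study, or that follow soon after. Once the patient is withdrawn, how completely later events are recorded depends on which section a site reads and how hard the investigator pursues the case.

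That investigator knows the allocation. The trial is open label and the investigator carries out the randomisation. Blinded assessment is described for clinical recovery and for several patient-centred measures, but not for event capture after withdrawal. If capture differs between sites or arms, an observed difference in ventilation, shock or death, or the absence of one, could not be read with confidence.

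**Working it through.** The plan gives no figure to reproduce here. The sample size is one of convenience: 70 + 70 = 140 per trial. The check compares the passages and then scales the result.

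**Step 1. Which events fall after withdrawal?** ICU admission, ventilation, respiratory failure, ARDS and shock are both triggers and outcomes. When one of them is the trigger, it is known at withdrawal. When the trigger is oxygen support, any ICU admission, ventilation, ARDS or shock comes later, and death will usually follow some trigger. In the 191-patient study in Table 2 of the literature review, the median times are 12 days to ICU, 14.5 to ventilation and 18.5 to death. Sepsis/shock, at 9 days, comes before ICU. These medians need not come from the same patients, so the order is only indicative.

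**Step 2. What is required after withdrawal?**

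| Source | Status | Content |
|---|---|---|
| Fig 1 note | Stated as done | Outcome, not specified further |
| Section 9, contact | Required but informal, to 12 weeks | Clinical developments. The list has severity, hospital days, discharge, recovery and death, but not ICU, ventilation, ARDS or shock |
| Section 9, Table 1 assessments | Encouraged | Scheduled assessments |
| Section 10 | Encouraged, to week 12 | Hospital management, illness course, final outcome, later health |
| Appendix K | Requested at withdrawal | ICU yes/no and a death box. Nothing for ventilation, ARDS or shock, and no dates tied to events |
| Appendix J | Daily in hospital; continuation after withdrawal not stated | Rows for ICU, ventilator, ARDS and shock, but columns end at D20 |
| Appendix P, serious adverse events | Mandatory up to the last visit the protocol requires | That visit is not defined for a withdrawn patient |

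No single source both requires collection after withdrawal and captures all the listed events with dates to Day 28.

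**Step 3. Scale.** Section 2 gives progression to the severe stage as under 20% and mortality as 2–3%, for COVID-19 generally. The 5% lower bound is an assumption.

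- Progressors per trial: 140 × 0.05 = 7 to 140 × 0.20 = 28, or 3.5 to 14 per arm.
- Deaths per trial: 140 × 0.02 = 2.8 to 140 × 0.03 = 4.2.
- If a fraction *u* of *m* progressors per arm has an unknown later outcome, the risk difference for an event can shift by up to ± *m* × *u* / 70.

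| *u* (assumed) | *m* = 3.5 | *m* = 14 |
|---|---|---|
| 10% | ±0.5 points | ±2 points |
| 20% | ±1 point | ±4 points |
| 30% | ±1.5 points | ±6 points |
| 50% | ±2.5 points | ±10 points |

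**Illustration only.** Suppose four patients in each arm are truly ventilated, with full capture in one arm and half in the other. The trial would report 4/70 = 5.7% against 2/70 = 2.9% with no true effect. Nothing in the documents predicts that degree of imbalance.

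**The case against.** Much can be said for the plan.

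- Section 9 asks for more than contact: investigators must also record clinical developments. Section 10 asks for hospital management and course of illness, which would naturally cover ICU and ventilation.
- Appendix K has boxes for ICU and death.
- Appendix P requires immediate reporting of fatal and life-threatening events in both arms, and the adverse event form has start and end dates.
- Section 10 says all patients are admitted, so hospital records will exist.
- The trial is exploratory and unpowered. Even 4/70 against 2/70 gives a Fisher p of about 0.68. It also excludes patients with severe disease or likely to worsen, so progression may be well below 20%.

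All of this stands, and it rules out several stronger readings that a reader might infer:

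- *All the severe outcomes are collected mainly after withdrawal.* Not so: a triggering event is known at that moment. The gap concerns death and later events.
- *Follow-up after withdrawal is merely optional.* Not so: Section 9 requires contact and recording, and Fig 1 is stated flatly.
- *The daily sheet stops at withdrawal.* No text says this. The documents are silent.
- *Both primary outcomes carry a 28-day frame.* Section 11.1 prints it only for time to recovery.

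What remains is that Section 10's request is only encouragement, Section 9's requirement is informal and names few of the events, the forms lack fields and dates, and the safety route has no defined end after withdrawal.

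**Conclusion.** The concern holds in this limited form. Progression takes patients out of the study, and the plan does not consistently require, or equip sites to record, dated severe events and deaths after that point. About 7 to 28 of 140 patients per trial would be affected at an assumed 5–20% progression. The possible shift in a risk difference runs from about half a point to ten points, depending on assumed progression and loss.

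The documents show that uneven, arm-aware ascertainment is possible. They do not show that it will occur or in which direction. The progression and mortality rates come from a broader population, and the loss fractions are assumptions.

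A related limit is that Section 17.2 admits patients to the intent-to-treat analysis only after four weeks of intervention and the week-4 visit. A patient withdrawn earlier could fall outside that set even if every event were recorded.

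**What to change.** Separate two things that the plan merges: stopping study treatment and leaving the study. Appendix B describes this distinction in the WHO trial it summarises, where patients may stop study treatment yet remain in the study.

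1. Reconcile the Fig 1 note, Sections 9 and 10 and stop rule 1 in Section 14, including whether withdrawal is mandatory or discretionary. Leave the clinical rules for stopping treatment to those responsible for them.
2. State that every randomised patient who has not refused further data use stays in outcome collection. This means daily extraction onto Appendix J while in hospital, with columns extended from D20 to D28; the existing app or telephone contact after discharge; and vital status and outcome to week 12.
3. Replace the encouraged and informal wording with a requirement. Add dated fields for ICU admission, ventilation, respiratory failure, ARDS, shock and death to the Section 9 list and Appendix K.
4. State how long serious adverse event reporting runs for these patients.

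The cost is a wording change, a small revision of two forms and extra chart extraction for the patients who progress, roughly 7 to 28 per trial. Section 8 expects most patients home within 5 to 15 days, so few others should need the added Appendix J columns. The Section 17.2 analysis-set condition should be checked at the same time, so that the data collected can be used.
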